#### Students

Trial measurement of 250 high school students to self-refer for randomization (in 2:1 ratio) to TMCU or waitlist/control includes baseline survey of demography, contact information, normative perceptions of marijuana use [60, 61], and life goals information [62] incorporated as personal feedback. Repeated-measures assessed in intervention outcome assessments (i.e., baseline, 3- and 6-month follow-up) include the following student-report instruments (1) Global Appraisal of Independent Needs [63], offering recent marijuana use and diagnostic symptoms; (2) Marijuana Problems Scale [64]; (3) Marijuana Motives Measure [65]; (4) self-efficacy to avoid marijuana use [66]; (5) Student Academic Self-Report, tapping homework completion, attendance, and disciplinary actions [67]; and (6) Student Engagement Instrument [68], measuring academic and social engagement. This will be supplemented by administrative data accessed from participating school districts. Students will receive financial remuneration to incentivize retention and completion of outcome assessments.

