#### Student randomization

Upon determination of eligibility, students will be randomized in a 2:1 ratio to TMCU or waitlist/control. This will occur after blocking by student gender and grade-level, independently at each school. The trial seeks 250 student participants during its 24-month period of TMCU implementation.

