#### Student outcome assessments

The trial coordinator will govern procedures for these assessments at 3- and 6-month follow-up points, for which the purpose is to evaluate TMCU’s clinical effectiveness. Students will similarly complete follow-up web-based assessments on encrypted internet server. Attrition will be minimized through use of extensive contact/locator information by research staff, who maintain networking relationships with local social service agencies. Similar procedures have led to 90+% retention rates in prior TMCU trials.

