### Hypothesis testing and analytic approach

Hypotheses focus on comparative utility of two technical assistance methods on implementation outcomes among TMCU interventionists and intervention effectiveness among students. Hypothesized effects are that the (1) longitudinal effects of interventionists receiving ‘gold-standard’ vs. ‘as-needed’ technical assistance will not differ, with the latter method proving more cost-beneficial and cost-effective; and (2) effects of technical assistance method for intervention impact on student marijuana use frequency will not differ, with greater reduction expected of students randomly assigned to TMCU vs. waitlist/control.

Trial analyses will be governed by an investigative team member (KK), experienced as a biostatistician and methodologist in adolescent health research. Given nesting of trial data (i.e., repeated observations of students, nested in interventionist caseloads; interventionists nested in schools), multilevel models will include progressive taxonomies in model-building. Initially, an unconditional model will estimate variance of random effects, and a subsequent unconditional growth model will identify the appropriate shape of and variability in rate of change over time for hypotheses involving repeated measures. Technical assistance condition will then be included in conditional models with predictors, with relevant covariates added to determine robustness of main effects and relative goodness-of-fit for each successive model via likelihood ratio tests and deviance statistics. Power analyses (.80, *p* < .05) inform proposed recruitment of (1) 30 interventionists to detect longitudinal effects of training and technical assistance consistent with those for other lay counselors (Cohen’s *d* = 1.00); and (2) 250 students to detect small intervention effects (Cohen’s *d* = .35) relative to waitlist/control.

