#### Hypothesis 1a: comparable utility of technical assistance methods

A non-inferiority paradigm, traditionally used to show a novel treatment is not statistically different than an established one, will test study hypotheses. This paradigm will be applied to interventionists’ longitudinal implementation outcomes, principally TMCU fidelity (i.e., R:Q, %OQ, %CR) in SP interactions but also secondary outcomes of TMCU knowledge, attitudes, adoption readiness, and satisfaction. Initial effects are consistent with training intent, with analyses testing if ‘gold-standard’ and ‘as-needed’ technical assistance produce equivalent longitudinal impacts. If (as expected) the number of schools recruited is small, they will be dummy-coded and treated as fixed effects. Point-estimates and confidence intervals from the model will be included in non-inferiority tests, examining each technical assistance method for (1) pre-post change in implementation outcomes, (2) mean implementation level by TMCU interventionists over time, and (3) differential rate of change in implementation over time. As recommended [75], a ½ standard deviation (SD) difference will serve as the a priori non-inferiority margin. If the lower bound of two-sided 95% confidence interval of between-method differences exceeds this margin, a test of superiority will specify the direction and magnitude of differential impact of the technical assistance methods.

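### At 2:1 allocation, 250 students give about 74% power for d = .35 in a conventional two-sided unadjusted comparison; the stated .80 needs conditions the article does not give

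*Protocol article*

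**What the plan says.** In the protocol article, the section Hypothesis testing and analytic approach gives the basis for both samples in one sentence: "Power analyses (.80, *p* < .05) inform proposed recruitment". For students, the number is "250 students to detect small intervention effects (Cohen’s *d* = .35) relative to waitlist/control". The hypothesis in that section is directional, "with greater reduction expected of students randomly assigned to TMCU vs. waitlist/control", but the sidedness of this test is not given.

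Under Student randomization, "students will be randomized in a 2:1 ratio to TMCU or waitlist/control". Under Student outcome assessments, the expectation for follow-up rests on past experience: "Similar procedures have led to 90+% retention rates in prior TMCU trials".

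The planned analysis is a multilevel growth model for "repeated observations of students, nested in interventionist caseloads; interventionists nested in schools". Student outcomes are measured at baseline, 3 and 6 months. Covariates enter late in model building, as a check on the robustness of the main effects. No within-student correlation or intraclass correlation is printed.

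**The concern.** The article prints a power, an alpha, an effect size, a total and an allocation ratio. Under the reading most statisticians would apply to such a sentence, these do not fit together. Unequal allocation costs precision: at a fixed total, the variance of the difference is 4.5/4 = 1.125 times as large at 2:1 as at 1:1. The printed total is close to what 1:1 would need and well short of what 2:1 would need.

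TMCU versus waitlist is the trial's effectiveness test, and the incremental cost-effectiveness ratio rests on it. If the true risk of missing d = .35 is 26% to 31% and not 20%, a null result deserves a more cautious reading than the article invites.

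**Working it through.** **Inputs from the article.** N = 250, d = .35, alpha .05, power .80, 2:1 allocation (about 167 TMCU, 83 waitlist). A 10% loss (150 and 75) is a scenario based on the prior-trial retention. Correlations and intraclass correlations below are assumptions.

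**The stated figure.** With SD = 1, SE = √(1/n₁ + 1/n₂). Power is taken from the noncentral t with noncentrality .35/SE.

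| Arms | SE | .35/SE | Two-sided power | One-sided power |
|---|---|---|---|---|
| 125 / 125 | .1265 | 2.767 | .787 | .867 |
| 167 / 83 | .1343 | 2.606 | .738 | .830 |
| 150 / 75 | .1414 | 2.475 | .693 | .795 |

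The two-sided calculation comes close to .80 only at 1:1 without loss. The one-sided calculation at 2:1 with 10% loss also comes close (.795).

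**Students needed for .80, two-sided.**
- 1:1: 4 × (1.96 + .84)² / .35² = 4 × 7.85 / .1225, about 257.
- 2:1: 4.5 × 7.85 / .1225, about 289 (291 when rounded to whole arms of 194 and 97).
- 2:1 with 10% loss: 289/.9 to 291/.9, so 321 to 324.
- 2:1, one-sided: 228, or 228/.9 = 254 with 10% loss.

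**Effect detectable with .80 power at 2:1, two-sided.** 2.80 × √(1/n₁ + 1/n₂) gives d = .376 at N = 250 and .396 at N = 225.

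**Whether repeated measures restore .80.** This depends on the contrast. Let r be the baseline to follow-up correlation, with d kept on the outcome SD.

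- *Linear growth slope over 0, 3 and 6 months.* The visit weights are proportional to −1, 0, +1, so with complete data the 3-month visit drops out and the contrast is the 6-month change score. Its variance factor is 2(1 − r).
- *One follow-up adjusted for baseline.* The variance factor is 1 − r².

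| r (assumed) | Change, N = 250 | Change, N = 225 | Adjusted, N = 250 | Adjusted, N = 225 |
|---|---|---|---|---|
| .4 | .659 | .614 | .809 | .767 |
| .5 | .738 | .693 | .850 | .812 |
| .6 | .827 | .787 | .901 | .869 |

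At N = 250 the variance factor must fall to .867 for .80 power. For the change score, 2(1 − r) = .867 gives r of about .57. For the adjusted contrast, 1 − r² = .867 gives r of about .36. At N = 225 the required factor is .780, so r is about .61 and .47.

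**Clustering.** Waitlist students receive no TMCU until 6 months have passed, so the assumed interventionist clustering is applied to the TMCU arm only. With 150/30 = 5 students per interventionist and an assumed intraclass correlation of .05, the design effect is 1 + 4 × .05 = 1.20. Unadjusted SE = √(1.20/150 + 1/75) = .1461, and power falls from .693 to .665. With baseline adjustment at r = .5, and the same design effect applied to the residual variance, SE = √.75 × .1461 = .1265 and power is .787 in place of .812.

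**The case against.** The best defence is that the trial does not plan an unadjusted test at one time point. It plans a multilevel model of three visits, and several contrasts within such a model reach .80. For example, with equal correlation among visits, the mean of the two follow-ups without baseline gives .85 at N = 250 and about .81 at N = 225 when r = .5 (normal approximation). The hypothesis is directional, and a one-sided .05 test at 2:1 with 10% loss needs 254 students, very near the printed 250. The one explicit statement of sidedness, the "two-sided 95% confidence interval of between-method differences", belongs to the technical-assistance comparison. This is also a condensed article, and the sidedness, correlation and attrition allowance may well sit in a fuller document.

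Much of this stands. A reader might infer that power simply is 74%, or that the 2:1 ratio was left out of the calculation. The article supports neither. The first depends on a two-sided unadjusted contrast that is not specified. The second rests only on the near match at 1:1, and the one-sided variant at 2:1 matches about as well. Nor is 90% retention a stated input to the power analysis; it is what similar procedures achieved before. The absence of these details from an article is not the point raised here.

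Two parts of the defence do not carry. A directional expectation is not a one-sided alpha, and nothing in the article declares one. And repeated measures are no automatic rescue: the growth-model route, read as a linear slope, has no more power than the unadjusted comparison unless r exceeds .5.

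**Conclusion.** The point holds in conditional form. With the printed inputs and 2:1 allocation, a two-sided unadjusted comparison has about 74% power at 250 students and about 69% after a 10% loss; .80 would need about 290, or 321 to 324 with that loss. The stated .80 is neither confirmed nor refuted for the analysis finally run, because it depends on sidedness, contrast and correlation. It is secure only under choices that the article does not print, and any positive clustering by interventionist works against it.

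This is a moderate point, not one on which the trial stands or falls. The gap under the conventional reading is 6 to 11 percentage points, and an analysis choice can close most or all of it with data already being collected.

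**What to change.** 1. Restate the student power for the 2:1 allocation and give its basis: sidedness, contrast and time point, attrition allowance, and assumed correlation and intraclass correlation. For a two-sided unadjusted comparison the statement would be about 74% power for d = .35, or 80% power for d of about .38 (.40 with 10% loss).

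2. Specify the primary TMCU versus waitlist contrast as adjusted for baseline marijuana use, with baseline as a covariate or constrained equal between arms, and not as a free change or growth-slope contrast. Baseline use is already measured: "Repeated-measures assessed in intervention outcome assessments (i.e., baseline, 3- and 6-month follow-up". In the table above, the adjusted contrast has more power than the change score at every correlation shown. Under an assumed r of .5 and a single follow-up it gives about 85% at N = 250 and 81% at N = 225 before clustering; with an assumed intraclass correlation of .05 in the TMCU arm the latter is about 79%.

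The cost is one restated power sentence and one line of analysis wording. No added enrolment and no new measurement are proposed.

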#### Hypothesis 1a: comparable utility of technical assistance methods

A non-inferiority paradigm, traditionally used to show a novel treatment is not statistically different than an established one, will test study hypotheses. This paradigm will be applied to interventionists’ longitudinal implementation outcomes, principally TMCU fidelity (i.e., R:Q, %OQ, %CR) in SP interactions but also secondary outcomes of TMCU knowledge, attitudes, adoption readiness, and satisfaction. Initial effects are consistent with training intent, with analyses testing if ‘gold-standard’ and ‘as-needed’ technical assistance produce equivalent longitudinal impacts. If (as expected) the number of schools recruited is small, they will be dummy-coded and treated as fixed effects. Point-estimates and confidence intervals from the model will be included in non-inferiority tests, examining each technical assistance method for (1) pre-post change in implementation outcomes, (2) mean implementation level by TMCU interventionists over time, and (3) differential rate of change in implementation over time. As recommended [75], a ½ standard deviation (SD) difference will serve as the a priori non-inferiority margin. If the lower bound of two-sided 95% confidence interval of between-method differences exceeds this margin, a test of superiority will specify the direction and magnitude of differential impact of the technical assistance methods.

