#### Interventionists

Trial measurement for 30 TMCU interventionists to be recruited (*n* = 2–4 per school) includes pre-training collection of demography (age, gender, ethnicity, race), professional background (educational attainment; setting tenure, role, duties), and prior MI exposure. Repeated-measures assessed in six training outcome assessments (i.e., pre/post-training; 6-, 12-, 18-, 24-month follow-up) are the survey-based Motivational Interviewing Knowledge and Attitudes Test [57] and Adoption Readiness Scale [58], which supplement an audio-recorded standardized patient (SP) interaction conducted in interventionists’ workspace and independently scored with a validated fidelity scale [59] by raters blinded to technical assistance condition. Post-training assessment specifically adds a web-based survey of training satisfaction, with follow-up assessments similarly tapping satisfaction with technical assistance and potential contamination between technical assistance methods. To aid planned cost analyses, interventionists will submit weekly time-logs to document effort in core implementation activities (i.e., hours spent recruiting students and delivering the intervention). Interventionists will receive financial remuneration to incentivize retention and completion of assessments.

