**Fig. 2 Fig2:**
[figure not shown]
CONSORT flow diagram for TMCU interventionists

The second EPIS phase involves preparation for school-based staff to serve as TMCU interventionists, for whom broad inclusion criteria should increase generalizability of trial findings. This includes their completion of a pre-training assessment, workshop training plus training cases, and a post-training assessment. Trained staff will then be randomized to one of two technical assistance methods.

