#### Post-training assessment

Upon training conclusion, interventionists complete a web-based survey assessment of MI knowledge and attitudes, adoption readiness, and training satisfaction. Additionally, interventionists will repeat the audio-recorded SP encounter to assess the impact of training on TMCU fidelity.

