#### Staff randomization

At training conclusion, the trial coordinator (LM) will allocate via urn randomization TMCU interventionists to receive technical assistance via (1) a ‘gold-standard’ weekly group session, or (2) ‘as-needed’ individual sessions triggered by fidelity drift alarm. A shared feature of both methods is the direct oversight of the TMCU purveyor (DW), who will monitor fidelity in review of session audio-recordings and provide numeric feedback to interventionists regarding behavioral fidelity indices (i.e., R:Q, %OQ, %CR). Notably, the technical assistance methods differ in format and anticipated frequency of occurrence, with differential cost expected.

The third EPIS phase focuses on TMCU implementation at participating schools over a 24-month period. This includes recruitment and randomization of self-referring students, baseline student assessment, TMCU delivery, fidelity-monitoring and technical assistance, and student outcome assessments (3-, 6-month follow-ups). To inform cost-benefit and cost-effectiveness analyses, both purveyor and interventionists complete weekly continual time-logs documenting effort in select activities. Figure 3 offers a CONSORT flow diagram depicting trial procedures for self-referring students.

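### Pre-post change is listed as a non-inferiority parameter for the technical assistance methods, although both training assessments precede randomization, so that test says nothing about assistance

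*Protocol article*

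**What the plan says.** All references are to the protocol article.

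- **Order of events.** The paragraph under Fig. 2 describes preparation as a pre-training assessment, the workshop and training cases, then "a post-training assessment. Trained staff will then be randomized to one of two technical assistance methods". The section 'Staff randomization' places allocation at the end of training, when the coordinator will "allocate via urn randomization TMCU interventionists to receive technical assistance via" one of the two methods.
- **Purpose of the post-training assessment.** Under 'Post-training assessment', "interventionists will repeat the audio-recorded SP encounter to assess the impact of training on TMCU fidelity".
- **Assessment series.** The section 'Interventionists' gives "Repeated-measures assessed in six training outcome assessments (i.e., pre/post-training; 6-, 12-, 18-, 24-month follow-up". Two assessments therefore precede randomization and four follow it. Table 2 uses the same split.
- **What is tested.** 'Hypothesis 1a' applies a ½ SD margin and a two-sided 95% confidence interval for between-method differences, "examining each technical assistance method for (1) pre-post change in implementation outcomes, (2) mean implementation level by TMCU interventionists over time", and lists as its third parameter "3) differential rate of change in implementation over time". It names no assessments for the mean and no time origin for the rate of change. It gives no rule for combining the three parameters.
- **Training versus assistance.** The same section says "Initial effects are consistent with training intent, with analyses testing if" the two methods have equivalent longitudinal impacts.

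**The concern.** For staff measures, the article uses pre/post only for the two training assessments and sets them apart from the 6-, 12-, 18- and 24-month follow-ups. On that reading the first listed parameter is complete before anyone is assigned to 'gold-standard' or 'as-needed' assistance. Randomization makes its expected between-method difference zero, so a pass is not evidence that the cheaper method preserves fidelity, and a failure is not evidence that it does not. Because the three parameters are unranked, a pass on this one could be reported as support for Hypothesis 1a.

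A related question is which assessments form the mean over time. Pre-randomization scores carry no assistance effect, so averaging them in pulls a real difference towards zero. In a superiority comparison that costs power. In a non-inferiority comparison it makes an unwarranted claim easier.

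**Working it through.** **The plan's own figure.** The only staff-level calculation stated is 30 interventionists for d = 1.00 at power 0.80 and p < .05 ('Hypothesis testing and analytic approach'). By the normal approximation, n per arm = 2 × (1.960 + 0.842)² / 1² = 15.7, so 16 per arm or 32 in total. With 15 per arm, power is Φ(1/√(2/15) − 1.960) = Φ(0.779) = 78%. The stated figure is reproduced closely and is not in dispute.

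**Inputs from the article:** 30 staff; margin 0.5 SD; two-sided 95% interval; two assessments before randomization and four after.

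**Assumptions not in the article:** 15 per arm; SD of a single assessment as the scale of the margin; equal within-person correlation ρ between any two assessments, taken as 0.3, 0.5 and 0.7; a constant deficit D from month 6; no dropout; no school effects. Results use the noncentral t with 28 df.

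**Step 1: pre-post training change.** The expected difference is 0 for every D. Its standard error is √(2/15) × √(2(1 − ρ)). Non-inferiority is declared when the lower bound lies above −0.5.

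| ρ | SE | P(non-inferiority declared), any D |
|---|---|---|
| 0.3 | 0.432 | 20% |
| 0.5 | 0.365 | 26% |
| 0.7 | 0.283 | 40% |

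These values do not move with D. They are the same at a deficit of 1 SD as at none.

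**Step 2: mean over time, by which assessments are averaged.** For k assessments, four of them after randomization, the expected difference is −(4/k)D and the standard error is √(2/15) × √((1 + (k − 1)ρ)/k). At a true deficit D = 0.5 SD, exactly at the margin:

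| Assessments averaged | Expected difference | False non-inferiority, ρ = 0.3 / 0.5 / 0.7 |
|---|---|---|
| Four follow-ups | −0.50 | 2.5% / 2.5% / 2.5% |
| Post-training plus four | −0.40 | 5.9% / 5.3% / 4.9% |
| All six | −0.33 | 10.1% / 8.3% / 7.3% |

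With all six averaged, the expected difference reaches the margin only when D = 0.5 × 6/4 = 0.75 SD.

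**Check.** A simulation of 40,000 trials at ρ = 0.5 and D = 0.5 gave 2.5% (four), 8.3% (six) and 26.1% (pre-post change).

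**Step 3: rate of change.** Take post-training as time zero and months 0, 6, 12, 18, 24. The deviations from month 12 are −12, −6, 0, 6, 12, with sum of squares 360. A constant deficit D at the four follow-ups gives a slope difference of D(−6 + 0 + 6 + 12)/360 = D/30 per month, or 0.8D over 24 months. With that origin a post-randomization deficit shows in the slope, so this parameter is informative about assistance.

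**The case against.** **Averaging all six assessments is an inference.** A reader might take the plan to average all six. The text says only over time. It attributes initial effects to training and compares longitudinal impacts, which points towards the follow-ups. Satisfaction with assistance exists only at the four follow-ups, so no six-assessment mean is possible for it. On the other side, the article defines the repeated measures as the six-assessment series and nothing in Hypothesis 1a excludes the first two. The dilution is a permitted reading, not a stated plan, and the full plan may settle it.

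**The tests as a whole are not shown to be biased.** A reader might also infer that the whole set of staff tests leans towards no difference and will produce false claims. That does not follow. The rate-of-change test is sound with post-training as time zero and would be distorted only if one slope ran through the pre-training score; the article leaves the shape of change to model-building. If all three parameters had to pass, the pre-post test would make the claim harder. Under equal correlation, pre-post change is independent of the six-assessment mean, so passing both at a true 0.5 SD deficit has probability 0.101 × 0.20 = 2.0%, 0.083 × 0.26 = 2.2% or 0.073 × 0.40 = 2.9%. The article states no such rule, but neither does it say that one pass suffices.

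**Pre-post might mean before versus after assistance.** That conflicts with the article's other uses of the term for staff and leaves the post assessment unnamed among four. The wording would still need correcting.

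What stands against these points is the first parameter. It is written into the article, so it is not a detail left to the analysis plan, and on the article's own terms assistance cannot affect it.

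**Conclusion.** The point holds for pre-post change. As a between-method non-inferiority parameter it is uninformative about Hypothesis 1a: its expected difference is zero whatever the assistance does, and it would pass about 20% to 40% of the time with 15 per arm and a correlation of 0.3 to 0.7. Uninformative is the exact word here, rather than biased.

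The point about the mean is conditional. Only if all six assessments were averaged would a constant deficit shrink to 4/6 and false non-inferiority at 0.5 SD rise from 2.5% to about 7% to 10%. Those percentages also depend on equal correlations, a margin scaled to a single-assessment SD (the article does not say which SD), the 15:15 split and no dropout. The documents do not establish that the rate-of-change test or the satisfaction outcome is affected.

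**What to change.** In 'Hypothesis 1a':

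1. Remove pre-post training change from the between-method non-inferiority tests and report it once, pooled over methods, as the effect of training.
2. Base the between-method mean comparison on the 6-, 12-, 18- and 24-month scores, adjusted for the post-training score as baseline. Satisfaction with assistance has no post-training value and is compared unadjusted.
3. Set post-training as time zero for the rate-of-change comparison.

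The cost is analysis wording. All the assessments are already scheduled, and 'Trial regulation and current status' says interventionist enrollment had not begun. Precision need not suffer. Under the same equal-correlation model, adjustment gives a variance factor of (1 + 3ρ)/4 − ρ² = 0.385, 0.375 and 0.285 at ρ = 0.3, 0.5 and 0.7, against (1 + 5ρ)/6 = 0.417, 0.583 and 0.750 for an unadjusted mean of all six. This ignores the small cost of estimating the adjustment.

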#### Hypothesis 1b: comparable clinical effectiveness of technical assistance methods

For student outcomes, multilevel models extend to three levels for repeated observation of marijuana use frequency and secondary outcomes (i.e., problems, motives, perceptions, self-efficacy to abstain, academic performance, and engagement) nested within interventionists. A primary test parameter is the interaction of time × technical assistance method of the TMCU interventionist as a dummy-coded predictor. As temporal effects may not conform to simple linear growth curves, models will test different specifications of time (i.e., piecewise, polynomial, or other nonlinear approaches). The a priori non-inferiority margin (i.e., ½ SD) will again be applied and, if exceeded, a test of superiority will specify the direction and magnitude of differential impact.

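### The ½ SD non-inferiority rule has no sign and, read literally, makes comparability the default unless a deficit beyond the margin is proven

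*Protocol article*

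**What the plan says.** The section on Hypothesis 1a introduces the non-inferiority paradigm as one "traditionally used to show a novel treatment is not statistically different than an established one". It then fixes the margin: "a ½ standard deviation (SD) difference will serve as the a priori non-inferiority margin". The decision rule is: "If the lower bound of two-sided 95% confidence interval of between-method differences exceeds this margin, a test of superiority" follows, and that test "will specify the direction and magnitude of differential impact of the technical assistance methods". The section does not say which method is subtracted from which, whether the margin is +½ or −½ SD, or what result would establish non-inferiority. The same margin serves three quantities: "1) pre-post change in implementation outcomes, (2) mean implementation level by TMCU interventionists over time, and (3) differential rate of change in implementation over time".

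The section on Hypothesis 1b carries the margin to student outcomes, with marijuana use frequency first: "The a priori non-inferiority margin (i.e., ½ SD) will again be applied and, if exceeded, a test of superiority" follows. It names no confidence limit. On the parameter it says: "A primary test parameter is the interaction of time × technical assistance method of the TMCU interventionist as a dummy-coded predictor".

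The end of the Background names the comparison of the two technical assistance methods, on implementation outcomes and on intervention effectiveness, as the co-primary aims. This rule therefore decides the trial's main claims.

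**The concern.** A non-inferiority test has to place the burden on the new method: as-needed assistance is accepted only when the data exclude a deficit as large as the margin. The rule as printed acts in the other direction. Its only trigger is a lower limit that exceeds the margin, and the consequence is a test that describes a difference. If the trigger is not met, no further step is given, and the hypothesis that the methods do not differ is left standing. A wide interval, which a small sample gives, then helps the hypothesis.

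Two other phrases point the same way. Hypothesis 1b says "if exceeded, a test of superiority will specify the direction and magnitude of differential impact", so passing the margin is treated as a sign of difference. The description of the paradigm quoted above treats the lack of a significant difference as if it were non-inferiority, which it is not.

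There are two lesser gaps. For marijuana use lower is better, so the harmful side of the interval depends on the order of subtraction, and that order is not given. And ½ SD is compared with levels, changes and a time × method parameter, although neither the SD nor the unit of time is named.

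**Working it through.** **Inputs from the article.** 30 interventionists, d = 1.00, power .80, p < .05 (Hypothesis testing and analytic approach). Margin ½ SD and two-sided 95% CI (Hypothesis 1a). Staff follow-ups at 6, 12, 18 and 24 months (Training outcome assessments). 250 students randomized 2:1, so about 167 receive TMCU (Student randomization). Student follow-ups at 3 and 6 months (Students).

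**Assumptions.** Interventionists split 15/15, SD = 1, normal intervals unless stated. Correlation between staff follow-ups r = .2 to .7. TMCU students split about equally between methods, with no clustering.

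**The plan's own figure.** Per arm, n = 2 × (1.96 + 0.84)² / 1.00² ≈ 15.7, so 16, or 32 in total. At 15 per arm the power is 0.78. The stated 30 is reproduced within two participants. It is a size for detecting a difference of 1.00 SD; the decision rule has no stated operating characteristic.

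**Literal rule, one measurement.** Take the difference as gold-standard minus as-needed, so that a deficit is positive.
- SE = √(2/15) = 0.365; half-width = 1.96 × 0.365 = 0.716.
- The lower limit exceeds 0.5 only if the estimate exceeds 0.5 + 0.716 = 1.216 SD.
- With a true deficit of 1.0: P(flagged) = Φ((1.0 − 1.216)/0.365) = 0.277, so 72% go unflagged.
- With a t-based half-width of 0.748 the estimate must exceed 1.248, P = 0.25, so 75% go unflagged.
- True deficits of 0.75 and 0.5 SD are flagged with probability 0.101 and 0.025.

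If the difference is as-needed minus gold-standard instead, the literal rule practically never flags a 1.0 SD fidelity deficit: Φ((−1.0 − 1.216)/0.365) = Φ(−6.07). The order used above is the one that favours the plan.

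**Literal rule, mean of four follow-ups.** SE = √((1 + 3r)/4) × 0.365.
- r = .2: SE = 0.231; P(flagged) = Φ(0.5/0.231 − 1.96) = 0.58; unflagged 42%.
- r = .7: SE = 0.321; P(flagged) = 0.34; unflagged 66%.

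**Conventional rule.** Non-inferior if the lower limit of as-needed minus gold-standard is above −0.5 SD.
- True deficit of 0.5 SD: passes with probability 0.025.
- True deficit of 1.0 SD: passes with probability 0.0004.

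**Same data, two readings.** Suppose the estimated deficit is 1.0 SD from one measurement. As gold-standard minus as-needed the CI is 0.284 to 1.716. The lower limit is below 0.5, so the literal rule does not act and comparability stands, although the interval excludes 0. With the sign turned, the lower limit is −1.716, far below −0.5, so the conventional rule finds non-inferiority not shown.

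**Direction for marijuana use.** SE = √(4/167) = 0.155. Suppose the difference is as-needed minus gold-standard and the true harm is +0.5 SD. The condition that the lower limit is above −0.5 is met with probability about 1.00. The condition that the upper limit is below +0.5 is met with probability 0.025. If the difference is gold-standard minus as-needed, the lower limit is the right one. The result therefore turns on a direction that the text does not give.

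**Time unit.** If the margin is ½ SD per unit of time, the student allowance over 6 months is 0.5 × 6/1 = 3 SD with time in months, 0.5 × 6/3 = 1 SD with 3-month waves, and 0.5 × 6/6 = 0.5 SD with the follow-up as one unit.

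**The case against.** The strongest answer is that the rule can be read as the ordinary sequence: the lower limit clears −½ SD, non-inferiority is concluded, then superiority is tested. That reading cannot be excluded, because the margin carries no sign. But the wording of Hypothesis 1b and the account of the paradigm favour the reversed reading, and a primary decision rule should not depend on which one the analyst picks. It is also true that the article never says comparability will be declared when the trigger is not met. It names no other outcome, however, so the 42–75% above are probabilities of going unflagged.

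A reader might go further in three ways that the article does not support.
- That the plan uses the wrong bound for marijuana use. Hypothesis 1b names no bound, and Hypothesis 1a names the lower one for interventionist outcomes only. That inference also needs the −½ SD reading, under which the charge of reversal falls. What stands is that the direction is not fixed.
- That the shape of time is chosen after seeing the contrast. The section Hypothesis testing and analytic approach selects the shape in an unconditional growth model and adds technical assistance condition afterwards.
- That the margin allows 3 SD in students, or 12 SD in staff (0.5 × 24 months). Both figures assume a margin per month, which is nowhere stated. An SD of slopes or an end-of-follow-up contrast would be coherent. What stands is that the SD and the time unit are unnamed.

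**Conclusion.** The point holds as a defect in a stated rule. The margin is unsigned, the literal trigger reverses the burden of proof, and the two possible readings can give opposite conclusions. The size is large at the planned number of interventionists: a true loss of one SD in fidelity would go unflagged in about 72–75% of trials with one measurement, or 42–66% with the mean of four. A correct rule lets a ½ SD deficit through 2.5% of the time. These figures rest on a 1:1 split, SD 1, near-normal intervals, the more favourable order of subtraction and the assumed correlations. The missing direction for marijuana use and the missing SD and time unit are gaps of definition in the same rule. They are not evidence that a wrong bound or a particular slope margin was chosen. The rule decides the co-primary comparison, so it should be corrected.

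**What to change.** State one rule for both hypotheses:
1. Define the difference as as-needed minus gold-standard, signed so that positive is better; reverse it for marijuana use and problems.
2. Conclude non-inferiority only if the lower limit of the two-sided 95% CI is above −½ SD. Otherwise report that non-inferiority was not shown.
3. Test superiority, against 0, only after non-inferiority has been concluded.
4. Before comparing the time × method contrast with the margin, express it as the model-implied difference at a named time point, or over the whole follow-up, in units of a named SD.
5. Delete the description of non-inferiority as the absence of a statistical difference.

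The cost is wording. The article reports that interventionist enrolment was still to come, so the change could be made before any outcome data. The multilevel model and the time × method parameter can stay; replacing them with another primary contrast is a design preference and is not needed here. The team should know that the corrected rule is demanding: with 15 per arm and no true difference, non-inferiority is shown with probability 0.28 from one measurement, or 0.34 to 0.58 from the mean of four (r = .7 to .2).
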